## Abstract

**Aims:**

Acute wheezing illnesses are among the most common reasons preschool‐aged children are admitted to hospital. Readmission rates are high, and novel preventive strategies are required. OM‐85 is an orally administered bacterial lysate that stimulates anti‐viral immune responses and reduces excessive airway inflammation associated with wheezing episodes. The aim of the Assessing the Reduction of Recurrent admissions using OM‐85 for the treatment of preschool Wheeze (ARROW) trial is to determine the efficacy of OM‐85 in preventing hospital readmissions in children admitted to hospital with preschool wheeze. The primary outcome is hospital admission due to an acute wheezing illness during the 12‐month treatment period. Secondary outcomes include the frequency and duration of wheeze episodes and the cost‐effectiveness of the intervention.

**Methods:**

ARROW is a decentralised, Phase 3 randomised, double‐blind, placebo‐controlled trial. We aim to recruit and follow‐up 870 children aged 1 to < 6 years. Participants are randomised to 3.5 mg of OM‐85 or placebo daily for the first 10 days of every month, for 12 months. Health professionals from over 40 hospitals participating in the Children's Inpatient Research Collaboration of Australia and New Zealand (CIRCAN) invite families to the ARROW trial. The ARROW central team organises enrolment, randomisation, medication distribution, and follow‐up, conducting these activities entirely remotely in Australia and both remotely and in‐person in New Zealand.

**Ethics and Dissemination:**

ARROW received ethics approval from The Royal Children's Hospital Human Research Ethics Committee in Australia and the Health and Disability Ethics Committee in New Zealand. Findings will be published in peer‐reviewed international journals.

**Trial registration:** ANZCTR: ACTRN12620001370998 (Registered on 21 December 2020).

## Introduction

1

Acute wheezing illnesses are a leading cause of hospital admission among preschool‐aged children worldwide [1, 2, 3]. Viral infections trigger 80%–90% of wheeze episodes [4]. International guidelines emphasise the lack of objective evidence of efficacious treatments for preventing preschool wheeze [5]. Available treatments have not been shown to reduce recurrent wheezing episodes in the preschool‐age population and have the potential to cause harm [5, 6, 7, 8, 9]. Accordingly, identifying effective strategies to prevent recurrent preschool wheeze is a key research priority [10], with increasing interest in interventions targeting host responses to viral triggers [11].

OM‐85 (Broncho‐Vaxom) is an oral preparation [12] containing lysates derived from 21 bacterial strains of 8 common bacterial respiratory pathogens, including *
Haemophilus influenzae, Streptococcus pneumoniae, Klebsiella pneumoniae, Klebsiella ozaenae, Staphylococcus aureus, Streptococcus pyogenes, Streptococcus viridans* and *Neisseria catarrhalis* [13].

The mechanism of action of OM‐85 centres on the gut‐lung immune axis [14]. OM‐85 binds to pattern‐recognition receptors on intestinal mucosa dendritic cells [14], activating an immune cascade leading to the migration of cells from innate and adaptive branches of the immune system to the lung mucosa, promoting an effective antiviral response [15]. T‐regulatory cells are mobilised to the lungs, correcting the T‐helper cell imbalance and excessive mucosal inflammation and hyperreactivity associated with wheeze episodes [16]. Over 30 years of post‐marketing surveillance indicate a good tolerability profile [17]. Commonly reported adverse events (AEs) are uncommon, mild, and transient, and include gastrointestinal complaints, cough and rash [18].

A 2006 Cochrane review found that, among children with recurrent respiratory tract infections (RTIs), treatment with OM‐85 was associated with a 35.9% relative reduction (95% confidence interval (CI), 22.4% to 49.5%) in acute RTIs compared with placebo [18]. A 2020 meta‐analysis and systematic review concluded that bacterial lysates are a safe and effective add‐on therapy in children with wheeze to reduce exacerbations; however, most studies were performed in school‐aged children [13]. One small, double‐blind, placebo‐controlled, randomised controlled trial (RCT) found that children treated with OM‐85 for 3 months experienced a reduction of 2.18 wheeze episodes over a 12 month period (95% CI, −3.22 to −1.13) compared to placebo, a 38% relative reduction, with weak evidence suggesting a reduction in hospital admissions [19]. Trial limitations included small sample size, group imbalances in baseline characteristics, and exclusion of children treated with inhaled corticosteroids. The need for additional large, high‐quality, double‐blind, placebo‐controlled, RCTs has been identified [20]. More specifically, sufficiently large studies are required to determine whether OM‐85 reduces recurrent hospital admissions due to preschool wheeze.

## Objectives

2

### Primary Objective

2.1

To determine the efficacy of OM‐85 for preventing hospital admissions due to an acute wheezing illness over 12 months in preschool‐aged children with recurrent wheeze and previous wheeze‐related hospital admission.

### Secondary Objectives

2.2

To assess the effect of OM‐85 on recurrent wheeze events in preschool‐aged children with reference to: the number of wheeze‐related hospital admissions; number and duration of wheeze episodes; time to readmission; health resource utilisation; cost‐effectiveness; lost productivity; anxiety; and quality of life over 12 months.

### Trial Design

2.3

ARROW is a Phase 3 multi‐centre RCT of a 12‐month course of OM‐85 or placebo in children aged 1 to < 6 years with recurrent wheeze resulting in at least one hospital admission. Participants are randomised in a 1:1 ratio to OM‐85 or placebo.

## Methods

3

### Trial Setting

3.1

ARROW is recruiting participants from over 40 hospitals participating in the Children's Inpatient Research Collaboration of Australia and New Zealand (CIRCAN). Participants are referred to the trial by site doctors and nurses, or by self‐referral. Recruitment, treatment, and data collection are conducted by the ARROW central team, based at Barwon Health, Geelong, Australia, and across seven sites in New Zealand (NZ). Participating units are listed on the trial webpage (https://circan.org/om‐85/).

### Eligibility Criteria

3.2

Eligibility criteria are shown in Table 1. Hospital admission is defined as a hospital stay of > 6 h from the time of triage to discharge. In 2009, Australia introduced the Four‐Hour National Emergency Access Target requiring 85% of patients to spend < 4 h in the Emergency Department (ED) from the time of arrival [21], and NZ introduced a target of 95% of patients being seen, treated, or discharged from the ED within 6 h [22]. Based on this, the CIRCAN members decided a definition of 6 h would capture all children requiring hospital admission, while minimising misclassification of children who spent significant time waiting due to a low triage category.

**TABLE 1 jpc70434-tbl-0001:** Eligibility criteria.

Inclusion criteria
Children aged 1 to < 6 years who in the preceding 12 months have had at least one hospital presentation lasting over 6 h with wheeze **and** at least 2 other episodes of wheeze or whistling in the chest on breathing out, lasting over 6 h, associated with laboured breathing. Parent(s) or legal guardian(s) of the child is/are able to understand the study requirements and willing to provide informed consent.
Exclusion criteria
Known adverse reaction or hypersensitivity to bacterial lysates or to any of the excipients in OM‐85 in accordance with the composition. Known anatomic alterations of the respiratory tract. Chronic respiratory diseases other than preschool wheeze/asthma. These include cystic fibrosis, chronic suppurative lung disease and chronic lung disease of prematurity, defined by a persisting oxygen requirement at a corrected gestational age of 40 weeks. History of malignancy, autoimmune disease, liver, or kidney failure. Treatment with immunosuppressant drugs including methotrexate, cyclosporine, or azathioprine within 30 days prior to enrolment in this trial. Treatment with OM‐85. Limited/no access to an internet connection and/or a phone. Unable to fulfil protocol follow up requirements for > 2 months (e.g., planned overseas travel with limited internet access). Another participant in the same household is concurrently enrolled in the ARROW Trial.

*Note:* For Inclusion criterion 1 hospital admission must have occurred after the age of 12 months. The 2 other episodes of wheeze may have occurred prior to 12 months of age, provided they occurred within the last 12 months.

### Recruitment

3.3

Potential participants are identified by clinicians at participating sites and are invited to learn more about the ARROW trial and express their interest in participating.

In Australia, doctors use a web application on their devices to refer participants to the ARROW central team (Figure 1), by submitting the family's contact details, minimising the burden on referring clinicians and improving recruitment efficiency. Clinicians provide trial information using a QR code accessed in the web application, linking families to an information video. Once referred, the ARROW team contacts the family by phone to screen eligibility, provide the Participant Information and Consent Form (PICF) and arrange a video conference (Figure 2). Before proceeding, the ARROW team verifies the child's identity and wheeze‐related hospital admission with the relevant hospital site. An ARROW doctor then assesses eligibility, obtains electronic consent from the child's parent or legal guardian, and finalises the enrolment process.

**FIGURE 1 jpc70434-fig-0001:**
[figure not shown]
Referral process for clinicians in Australia.

**FIGURE 2 jpc70434-fig-0002:**
[figure not shown]
Study procedures in Australia and New Zealand. 
*Note:* Pre‐screening, information sharing and consent are done remotely in Australia, and either remotely or in person in New Zealand. Consent is completed by doctors in Australia and by nurses in New Zealand. Confirmation of eligibility is always completed by a doctor.

In New Zealand, nurses at each participating site engage with eligible families in person or remotely, providing relevant trial information. The consent and enrolment process is managed and completed by nurses, and a doctor completes the eligibility assessment.

In both countries, the QR code available through the web application, study posters, and information brochures links families to a short study information video and an expression of interest form, allowing for self‐referral. In Australia, families can also access the video and self‐referral form via social media advertisements.

Education and resources are provided to clinicians at participating sites, and engagement is maintained through regular meetings, newsletters, education sessions, and email communications.

### Randomisation

3.4

Following consent, participants are randomised to either OM‐85 or placebo in a 1:1 ratio, using the Griffith Randomisation System, a web‐based randomisation program [23], in a blinded fashion. The system utilises block randomisation, with variable block sizes, stratified by < 2 versus ≥ 2 admissions for wheeze in the preceding 12 months (including the index admission), age < 3 years or ≥ 3 years, and pharmacy location (Geelong or Auckland). The treatment allocations and block size will be concealed from all participants, trial investigators and research staff until the trial's completion, unless unblinding is required for compelling medical or safety reasons. Pharmacists dispensing the trial medication can unblind participants if required, with all unblinding events recorded in the study database.

### Intervention

3.5

Participants are provided with capsules containing either 3.5 mg of OM‐85 or a placebo, equal in appearance. The contents of one capsule are administered orally on an empty stomach daily for the first 10 days of each calendar month, for a total of 12 months (120 capsules). Capsules can be opened and their contents poured into a drink, such as milk, water, or fruit juice. Other routine treatments for wheeze can be continued, as determined by the child's treating team, and are not contraindicated during the trial (Table 1). With ongoing parent and community engagement and feedback, we have implemented multiple strategies to maximise participant engagement in the trial and adherence with the study medication and symptom reporting, including text reminders on treatment days and a calendar with stickers to engage participating children. Adherence with the trial medication is defined as the parental report of the participant receiving at least seven doses per month for at least 10 months. Parental report of the number of doses given each month of the study period will be consolidated with the number of remaining capsules reported by parents at the end of the trial.

### Data Collection

3.6

Data are collected for each participant recruited to the trial as described in Table 2. Participant data are stored using REDCap, a secure web‐based data capture tool [29] hosted by Deakin University, and are only available to research team members as required for their delegated role. Parents or guardians of participating children are sent links to complete the baseline survey, weekly electronic diaries, adherence surveys, and the end‐of‐study survey through REDCap. When a parent/guardian indicates on the electronic diary that their child presented to hospital with a wheeze episode, the ARROW team collects data from the hospital, including admission and discharge time and treatment details. Data are collected for the trial duration, defined as 12 calendar months after commencement of the trial medication. In addition to internal data quality assurance processes, an external monitor completes regular, independent reviews to minimise missing data and ensure data integrity. Incomplete surveys and data collection tools are followed up with participants directly throughout and at the end of the trial, including for participants who have discontinued the study medication for any reason.

**TABLE 2 jpc70434-tbl-0002:** Data collected for each participant.

Data collection tool	Timing of completion	Description
Baseline survey	Completed once at start of trial	Demographic information, height, and weight Medical, family, allergy history and social history Completed by parent/guardian
Test for Respiratory and Asthma Control in Kids (TRACK) [24]	At start and end of trial	Validated tool to measure asthma control Completed by parent/guardian
Food Frequency Questionnaire (FFQ) [25]	At start of trial	Information regarding child's diet
Child Behaviour Checklist (CBCL) [26]	At start and end of trial	Validated tool to assess behavioural and emotional problems including anxiety Completed by parent/guardian
Electronic diary	Weekly for duration of trial	Questions about medication changes and symptoms of wheeze If symptoms of wheeze, further questions about health care utilisation, treatment required, details of any hospital admissions, parental time off work, and so forth. Completed by parent/guardian
Adherence survey	Monthly after completion of 10‐day course of trial medication	Number of doses of study medicine administered Side effects of study medication (adverse events) Completed by parent/guardian
Adverse event form	Completed after every reported adverse event (AE) and/or serious adverse event (SAE)^a^	Details of potential AE or SAE, treatment required, outcome, and action required by ARROW team
Hospital survey	Completed after every hospital admission during the trial period	Timing and duration of admission, severity, treatment required and so forth. Data obtained from Principal Investigator at participating hospital, or medical records department if admitted to non‐participating hospital
End of study survey	Completed at end of trial	Child's height and weight Qualitative data regarding family's experience of the trial and suggestions for translating findings into practice
Questionnaires to assess quality of life of parent (EQ5D) [27] and child (PedsQL) [28]	Completed at end of trial	Validated quality of life surveys Completed by parent

^a^
Adverse events are reported by participants through monthly adherence surveys, and by phone or email directly to the ARROW team.

### Safety Monitoring

3.7

AEs and adherence are reported through weekly surveys or by participants contacting the ARROW team by email or telephone. Assessment of reported AEs is completed by ARROW paediatric doctors and Principal Investigators (PIs), as per the trial Protocol and Safety Monitoring Plan. The PI team may advise that the study medication be withheld or ceased due to concerns about possible AEs, or parents may elect to discontinue for any reason. Participants who discontinue their medication are invited to remain in the trial.

An independent Data and Safety Monitoring Board (DSMB) has been appointed to provide safety oversight and comprises two paediatricians, one respiratory paediatrician, and one biostatistician. The DSMB meets at least annually to review trial safety data and fulfil an advisory role as outlined in the DSMB charter. The trial would only be stopped early based on safety rather than efficacy considerations.

### Outcomes

3.8

The primary outcome measure is the proportion of participants with a hospital admission (hospital stay lasting > 6 h from the time of triage to discharge) due to an acute wheezing illness over a 12‐month period. Secondary outcomes are shown in Table 3. The 12‐month study period commences on the first day of treatment with the study medication rather than randomisation to allow time for participants to obtain the trial medication and to maintain a consistent treatment and study period for all participants. Commencement of the study medication is deferred where appropriate, for example, in the setting of intercurrent illnesses. If commencement is deferred for more than 3 months, eligibility is reassessed.

**TABLE 3 jpc70434-tbl-0003:** Outcome measures.

Primary outcome
Whether the child has a hospital admission due to an acute wheezing illness in the 12‐month period following commencement of the study medication (the study period). A hospital admission is defined as a hospital stay lasting longer than 6 h from the time of triage to the time of discharge.
Secondary outcomes
Time from initiation of the study intervention to subsequent hospital admission due to an acute wheezing illness within the 12‐month study period. Number of hospital admissions (> 6 h from triage to discharge) due to an acute wheezing illness per child over the 12‐month study period. Illnesses resulting in admission are considered discrete if the patient was without symptoms for at least 72 h between the end of one episode and the beginning of the next. Number of wheeze episodes per child over the 12‐month study period. A wheeze episode is defined as a wheezing illness resulting in repeated administration of an inhaled bronchodilator. Once again, illnesses are considered discrete if the patient was without symptoms for at least 72 h between the end of one episode and the beginning of the next. Total cost of health resource utilisation (hospital, community, pharmaceuticals) per child over the 12‐month study period. Parent or guardian loss of productivity (days of work missed/days out of role) over the 12‐month study period. Cost‐effectiveness of the intervention over the 12‐month study period. Mean duration of wheeze episodes (mean per child are used to calculate the group mean) within the 12‐month study period. Quality of life of the child using the PedsQL [28]; and parents using the EQ5D [30] at the end of the 12‐month study period. Anxiety symptoms in child using the Child Behaviour Checklist (CBCL) [26] at the end of the 12‐month study period.

### Sample Size

3.9

Prior to trial commencement, the most recently published data suggested an annual readmission rate for preschool wheeze of approximately 20% [31]. ARROW was powered to identify a 25% reduction in this rate, which CIRCAN investigators nominated as the minimum effect size required to change current practice. This required 1814 participants (907 per treatment group) based on a two‐sided chi‐squared test with 80% power and an alpha level of 0.05. Allowing for a 20% loss to follow‐up, we planned to recruit 2268 participants (1134 participants per group). However, as of March 2024, the ARROW participants' observed readmission rate for wheezing illnesses over 12 months was 33%, possibly reflecting the recruitment of children with relatively more severe preschool wheeze. This is consistent with a 2023 cohort study reporting a 12‐month readmission rate among children with asthma aged 3–18 years of 34% [32]. Given this, in 2024, we recalculated the required sample size assuming a 35% readmission rate in the placebo group. Retaining a 25% reduction in the admission rate as the minimum effect size needed to change practice (down to 26.25%), we recalculated the required sample size to be 870 participants (435 per treatment group). Allowing for 20% loss to follow‐up, we aimed to recruit 1088 participants (544 per treatment group).

### Statistical Methods

3.10

Data collection and reporting will follow the CONSORT guidelines, and analyses will be conducted according to the intention‐to‐treat principle, using a treatment policy strategy for all intercurrent events, as detailed in the statistical analysis plan (SAP). The estimand of interest for the primary outcome (hospital admission for wheeze within 12 months) is the odds ratio for OM‐85 compared with placebo, which will be estimated via logistic regression adjusted for stratification factors (age group, number of admissions, and pharmacy location reflecting the country of enrolment). There are no planned interim analyses. Missing data will be managed as per the study protocol and SAP.

The estimand of interest for the binary secondary outcomes is the (adjusted) odds ratio estimated as for the primary outcome. The estimand of interest for the time to readmission is the hazard ratio for the treatment effect, which will be estimated using a Cox Proportional‐Hazards model, censoring participants with no readmissions at the end of the 12‐month follow‐up, adjusted for the stratification factors. The estimand of interest for the number of readmissions and wheeze episodes is the incidence rate ratio, which will be estimated via Poisson regression adjusted for the stratification factors. The estimand of interest for the secondary outcomes of health resource utilisation, parent/guardian loss of productivity, duration of wheeze episodes and parent and child quality of life will be the difference in means between the treatment groups estimated using linear regression adjusted for the stratification factors. All results will be presented with 95% CIs and corresponding *p* values.

The primary economic analysis will be a cost‐effectiveness analysis from a healthcare perspective, comparing the difference in the primary outcome measure with the difference in costs between groups. Costs include the cost of OM‐85 and direct costs of all health service use, including hospital visits, community health services and pharmaceutical use. The secondary economic analysis will assess the impact of the intervention on families including parent‐reported out‐of‐pocket costs, loss of productivity and quality of life outcomes, through a cost‐consequences analysis from a societal perspective that compares the impact of OM‐85 on all measured outcomes to the difference in all costs (to health system, work, and family).

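### The primary logistic model could also use baseline TRACK, which the trial already collects: a cheap, modest gain in power, not an error in the plan

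*Protocol article*

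**What the plan says.** Section 3.10 (Statistical Methods) of the Protocol article estimates the primary odds ratio by "logistic regression adjusted for stratification factors (age group, number of admissions, and pharmacy location reflecting the country of enrolment"). Section 3.4 (Randomisation) shows how those factors are coded. Allocation is "stratified by < 2 versus ≥ 2 admissions for wheeze in the preceding 12 months", and by "age < 3 years or ≥ 3 years, and pharmacy location (Geelong or Auckland"). The model therefore carries three two-level covariates.

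Table 2 in section 3.6 (Data Collection) lists the "Test for Respiratory and Asthma Control in Kids (TRACK"), described as a "Validated tool to measure asthma control", with timing "At start and end of trial". TRACK is not among the outcomes in Table 3, nor in any model described in section 3.10.

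Section 3.9 (Sample Size) bases the numbers on a "two‐sided chi‐squared test" with 80% power and alpha 0.05. It retains a 25% relative reduction, from 35% to 26.25%, and arrives at 870 participants (435 per group), or 1088 after allowing for 20% loss. No gain from covariate adjustment is assumed.

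**The concern.** In a randomised trial with a binary outcome, adjusting for a baseline variable that predicts the outcome raises the power of the treatment test in a logistic model. Control of wheeze at entry is a plausible predictor of readmission for wheeze, and the trial already asks families for it. Eligible age spans 1 to under 6 years and prior admissions are a count, so the two-level splits also discard some information.

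The revised target sits at 80% power with essentially no margin. Efficiency that can be had from existing data, without recruiting more children, is therefore worth considering while the choice can still be made blind.

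**Working it through.** **1. Reproduce the plan's figure.** Inputs from section 3.9: p1 = 0.35, p2 = 0.2625, two-sided alpha 0.05, power 80%. With mean p = 0.30625:

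n per group = [1.960 × √(2 × 0.30625 × 0.69375) + 0.842 × √(0.35 × 0.65 + 0.2625 × 0.7375)]² / 0.0875² = 434.4, rounded up to 435.

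So 2 × 435 = 870, and 870 / 0.8 = 1087.5, rounded up to 1088. Both match. At 435 per group the unadjusted power is 80.05%.

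**2. Simulate the planned model and the alternatives.** Each scenario used 6,000 trials of 435 per arm, with marginal risks calibrated to 35% and 26.25% and a Wald test on the treatment term.

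Assumptions not in the documents:
- Age is uniform over 1 to 6 years.
- Admissions are 1 + Poisson(0.7), capped at 4 in the model.
- 30% of children are at one pharmacy location.
- TRACK is standard normal and independent of the other covariates.
- Age and admissions act linearly on the log-odds, with coefficients of 0.2 (weaker) or 0.35 (stronger) per roughly one SD.

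The effective-size ratio is (mean z with TRACK / mean z with strata only)².

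| Age and admission effects | TRACK log-odds per SD | TRACK AUC | Power, strata only | Power, strata + TRACK | Gain (points) | Effective-size ratio |
|---|---|---|---|---|---|---|
| weaker | 0 | 0.50 | 80.4% | 80.4% | 0.0 | 1.000 |
| weaker | 0.20 | 0.555 | 81.0% | 81.1% | 0.1 | 1.006 |
| weaker | 0.35 | 0.595 | 80.8% | 81.4% | 0.6 | 1.025 |
| weaker | 0.50 | 0.632 | 79.8% | 81.7% | 1.9 | 1.049 |
| weaker | 0.75 | 0.688 | 79.6% | 83.5% | 3.9 | 1.109 |
| stronger | 0 | 0.50 | 81.4% | 81.4% | 0.0 | 1.000 |
| stronger | 0.20 | 0.554 | 80.7% | 81.2% | 0.5 | 1.009 |
| stronger | 0.35 | 0.592 | 81.5% | 82.2% | 0.7 | 1.019 |
| stronger | 0.50 | 0.626 | 81.3% | 83.1% | 1.8 | 1.048 |
| stronger | 0.75 | 0.683 | 81.5% | 85.0% | 3.5 | 1.099 |

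Simulation error is √(0.8 × 0.2 / 6000) ≈ 0.5 point per power figure. The models in a row are fitted to the same data sets, so the gains are more precise than that.

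**3. Cross-check the top of the range.** 435 × 1.109 ≈ 482 per group. The unadjusted power formula gives 83.8% at 480 and 84.2% at 485, about 4 points above 80.05%. This agrees with the simulated gain.

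**4. Separate the two ideas.** Replacing the two-level age and admission terms with continuous ones, without TRACK, gained 0.0 to 0.9 point (0.4% to 1.7% in effective size). With continuous terms and TRACK together, the ratio ran from 1.004 to 1.115. Nearly all of any material gain comes from TRACK.

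**5. Correlated TRACK and type I error.** With TRACK correlated 0.4 with admissions, a further simulation still showed gains of 1.3 to 2.2 points. A separate null simulation of 4,000 trials gave 4.7% type I error for both the strata-only model and the model with TRACK and continuous terms.

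**6. Effect on the odds ratio.** The marginal odds ratio is (0.2625 / 0.7375) / (0.35 / 0.65) = 0.66. The odds ratio conditional on all covariates ranged from about 0.62 to 0.66 in the simulations.

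**The case against.** The strongest case against is that the plan is sound as it stands. The model matches the randomisation, and the sample size reaches its stated power without covariates. A full statistical analysis plan exists but is not shown, and it may name further covariates or supplementary adjusted analyses. All of this stands, and it is why the point is an improvement on offer rather than a fault.

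The benefit also rests on assumed inputs. The article gives no link between TRACK and readmission. Every enrolled child has had an admission and at least two other wheeze episodes within 12 months (Table 1), so baseline control may vary little. That stands too: the range includes zero. But when TRACK was uninformative, power was unchanged.

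Three practical cautions are fair:
- Table 2 places TRACK at the start of the trial, but does not say before the first dose.
- Section 3.6 describes following up incomplete surveys, so complete baseline TRACK cannot be taken for granted.
- Section 3.4 needs only fewer than two versus two or more admissions, and the article does not say that an exact count is recorded.

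These shape the recommendation without defeating it. Lastly, the odds ratio is non-collapsible, so adding a covariate changes the conditional quantity estimated. That is a real, small cost, but the planned odds ratio is already conditional on the strata.

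**Conclusion.** The point holds as an inexpensive improvement to a valid analysis. Adding baseline TRACK to the stratification factors would raise power by about 0 to 4 points with 870 evaluable children, equal to about 0% to 11% more participants (at most 0.109 × 870 ≈ 95 children). This assumes a TRACK AUC of 0.50 to 0.69 and independence from the other covariates. The gain would be smaller with correlation.

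A reader might infer more than this, and the documents do not support it:
- **That the primary analysis is wrong or underpowered.** It is neither; 435 per group gives 80.05% unadjusted.
- **That the gain is worth 10% to 15% more participants.** Only the most favourable assumed strengths approach this; weak to moderate ones give roughly 0% to 5%.
- **That the two-level coding costs much.** Undoing it adds at most about 1 point.
- **That TRACK is used nowhere.** The article states no such use, but the analysis plan is not shown.
- **That the Cox, count and linear secondary models would gain equally.** This was not calculated.

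**What to change.** Before unblinding, pre-specify the primary model as logistic regression on treatment, the three stratification factors and baseline TRACK as a continuous score. Count only TRACK values completed before the first dose as baseline, and treat later ones as missing. Fill missing baseline values by a simple rule that ignores treatment, such as the overall mean, so that no child is dropped. Continuous age may be added, as may the number of admissions if an exact count is recorded, but neither is needed for most of the gain.

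State that the odds ratio is conditional on this covariate set, report a standardised risk difference beside it, and keep the strata-only model as a sensitivity analysis.

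The cost is a short amendment to the analysis plan and a little more reporting. No new participants are needed, and no new data collection so long as TRACK is completed before the first dose. The downside is an odds ratio that conditions on one more variable than the one now described.
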